### 2.3.2 Benefit Assessment

This study being the first clinical evaluation of XVR011 in patients, there is no clinical data available yet regarding the therapeutic effect of XVR011 in patients with COVID-19.

The aim of treatment with XVR011 is to neutralise the virus, to reduce the severity of the disease, and to prevent progression to severe complications such as ARDS or other major organ dysfunctions.

Non-clinical data are available, which show significant reduction in viral load in an animal model (Syrian Golden Hamster) of SARS-CoV-2 infection, as well as *in vitro* data which show neutralisation of the virus, including the Delta VOC. All dose levels being evaluated in this study have been selected to have a potential clinical efficacy. See Section 4.3.

### 2.3.3 Overall Benefit: Risk Conclusion

Taking into account the measures taken to minimise risk to subjects participating in this study, the potential risks identified in association with XVR011 are justified by the anticipated benefits that may be afforded to subjects with COVID-19.

### 3 Objectives and Endpoints

**Table 3–1 Objectives and Endpoints for Part 1**

| PART 1 Objectives                                                                                                          | PART 1 Endpoints                                                                                                                                                                                                                                                                                                                                                                                                                                                                                                                                                                                                                                                                                                                                                          |
|----------------------------------------------------------------------------------------------------------------------------|---------------------------------------------------------------------------------------------------------------------------------------------------------------------------------------------------------------------------------------------------------------------------------------------------------------------------------------------------------------------------------------------------------------------------------------------------------------------------------------------------------------------------------------------------------------------------------------------------------------------------------------------------------------------------------------------------------------------------------------------------------------------------|
| Primary
To evaluate the safety of a single intravenous XVR011 infusion in subjects hospitalised for COVID-19     | 
 
• Proportion of subjects with Grade <math>\geq 3</math> treatment-related AEs within 28-day FU period
 
• Proportion of subjects with AEs (all and serious) of any grade and independent of causality within 28-day FU period
 
• Proportion of subjects with infusion-related reactions within 24 hours of treatment
 
• Proportion of subjects with hypersensitivity reactions within 28-day FU period
 
                                                                                                                                                                                                                                                                                           |
| Secondary
To evaluate the efficacy of a single intravenous XVR011 infusion in subjects hospitalised for COVID-19 | 
 
• Time to recovery (i.e., clinical status reaching level 1 to 3 of the 8-point ordinal scale) within 28-day FU period
 
• Total duration of oxygen supplementation within 28-day FU period
 
• Proportion of subjects requiring mechanical ventilation within 28-day FU period
 
• Proportion of subjects requiring ICU transfer within 28-day FU period
 
• Time to hospital discharge
 
• Proportion of subjects with clinical status evolving to each level of the 8-point ordinal scale at Days 2, 3, 4, 8, 15, 22 and Day 29, compared to baseline
 
• Proportion of subjects with COVID-19 related symptoms
 
• All-cause mortality rate within 28-day FU period
 
 |
| To evaluate the antiviral activity of a single intravenous XVR011 infusion in subjects hospitalised for COVID-19           | 
 
• Change from baseline (Day 1 pre-dose) in the viral load (RT-qPCR) of nasopharyngeal samples at Day 1, Day 3, Day 8 and day of discharge
 
                                                                                                                                                                                                                                                                                                                                                                                                                                                                                                                                                                               |

| PART 1 Objectives                                                                                                                                | PART 1 Endpoints                                                                                                                                                                                                                                                                                                                                                              |
|--------------------------------------------------------------------------------------------------------------------------------------------------|-------------------------------------------------------------------------------------------------------------------------------------------------------------------------------------------------------------------------------------------------------------------------------------------------------------------------------------------------------------------------------|
| Exploratory
To evaluate the effect of a single intravenous XVR011 infusion on disease biomarkers in subjects hospitalised for COVID-19 | 
 
Blood biomarkers (including but not limited to CRP, LDH, D-dimers, fibrinogen, absolute neutrophil count, lymphocyte count) at baseline (Day 1 pre-dose), on Days 2, 3, 4, 8, 15, 22 and on day of discharge
 
Optional blood sample for future exploratory biomarker testing at baseline (Day 1 pre-dose) and Day 3
 
 |
| To evaluate the pharmacokinetics (PK) of XVR011, following a single intravenous infusion in subjects hospitalised for COVID-19                   | 
 
Blood concentrations of XVR011 and PK parameters (<math>C_{max}</math>, AUC, <math>t_{1/2}</math>) on Days 1, 2, 4, 8, 15 and Day 29.
 
                                                                                                                                                                                       |
| To evaluate the immunogenicity of XVR011, following a single intravenous infusion in subjects hospitalised for COVID-19                          | 
 
ADAs and nAbs at baseline (Day 1 pre-dose), Day 15, and Day 29
 
                                                                                                                                                                                                                                                              |

ADA = anti-drug antibody; AE = adverse event; AUC = area under the plasma concentration-time curve;  $C_{max}$  = maximum observed plasma concentration; COVID-2019= coronavirus disease 2019; CRP = C-reactive protein; FU = follow-up; ICU = intensive care unit; LDH = lactate dehydrogenase; nAb = neutralising anti-drug antibody; RT-qPCR = reverse transcriptase quantitative polymerase chain reaction;  $t_{1/2}$  = apparent plasma terminal elimination half-life.

**Table 3–2 Objectives and Endpoints for Part 2**

| PART 2 Objectives                                                                                                                                                  | PART 2 Endpoints                                                                                                                                                                                                                                                                                                                                                                                                                                                                                                                                                                                                                                                                                                                                                                                                                                                                                                                                            |
|--------------------------------------------------------------------------------------------------------------------------------------------------------------------|-------------------------------------------------------------------------------------------------------------------------------------------------------------------------------------------------------------------------------------------------------------------------------------------------------------------------------------------------------------------------------------------------------------------------------------------------------------------------------------------------------------------------------------------------------------------------------------------------------------------------------------------------------------------------------------------------------------------------------------------------------------------------------------------------------------------------------------------------------------------------------------------------------------------------------------------------------------|
| 
Primary
 
To evaluate the efficacy of a single intravenous XVR011 infusion in subjects hospitalised for COVID-19, compared to placebo
           | 
 
Time to sustained recovery (i.e., clinical status reaching level 1 to 3 of the 8-point ordinal scale) within 28-day FU period; where recovery must be confirmed to be maintained at level 3 or lower for 14 consecutive days
 
                                                                                                                                                                                                                                                                                                                                                                                                                                                                                                                                                                                                                                                                              |
| 
Secondary
 
To further evaluate the efficacy of a single intravenous XVR011 infusion in subjects hospitalised for COVID-19, compared to placebo
 | 
 
Proportion of subjects who are alive and do not require any form of mechanical ventilation a at Day 8
 
Proportion of subjects requiring any form of mechanical ventilation a within 28-day FU period
 
Proportion of subjects requiring ICU transfer within 28-day FU period
 
Time to sustained hospital discharge (i.e. discharge with no re-hospitalisation after initial discharge for treatment of COVID-19 related events in the following 14 days) within the 90 day FU period
 
Total duration of oxygen supplementation within 28-day FU period
 
Proportion of subjects with clinical status evolving to each level of the 8-point ordinal scale at Days 2, 3, 4, 8, 15, 22 and Day 29, compared to baseline
 
Proportion of subjects with COVID-19 related symptoms
 
All-cause mortality rate within 28-day FU period
 
 |
| 
To evaluate the antiviral activity of a single intravenous XVR011 infusion in subjects hospitalised for COVID-19, compared to placebo
                       | 
 
Change from baseline (Day 1 pre-dose) in the viral load (RT-qPCR) of nasopharyngeal samples at Day 1, Day 3, Day 8 and day of discharge
 
                                                                                                                                                                                                                                                                                                                                                                                                                                                                                                                                                                                                                                                                                                                                                                   |

| PART 2 Objectives                                                                                                                                | PART 2 Endpoints                                                                                                                                                                                                                                                                                                                                                                                                                                                        |
|--------------------------------------------------------------------------------------------------------------------------------------------------|-------------------------------------------------------------------------------------------------------------------------------------------------------------------------------------------------------------------------------------------------------------------------------------------------------------------------------------------------------------------------------------------------------------------------------------------------------------------------|
| To evaluate the safety of a single intravenous XVR011 infusion in subjects hospitalised for COVID-19, compared to placebo                        | 
 
Proportion of subjects with Grade <math>\geq 3</math> treatment-related AEs within 28-day FU period
 
Proportion of subjects with AEs (all and serious) of any grade and independent of causality within 28-day FU period
 
Proportion of subjects with infusion-related reactions within 24 hours of treatment
 
Proportion of subjects with hypersensitivity reactions within 28-day FU period
 
 |
| Exploratory
To evaluate the effect of a single intravenous XVR011 infusion on disease biomarkers in subjects hospitalised for COVID-19 | 
 
Blood biomarkers (including but not limited to CRP, LDH, D-dimers, fibrinogen, absolute neutrophil count, lymphocyte count) at baseline (Day 1 pre-dose), on Days 2, 3, 4, 8, 15, 29 and on day of discharge
 
Optional blood sample for future exploratory biomarker testing at baseline (Day 1 pre-dose) and Day 3
 
                                                                                           |
| Additional evaluation of COVID-19 symptoms during the extended follow up period.                                                                 | 
 
COVID-19 related symptoms on Day 60 and Day 90
 
                                                                                                                                                                                                                                                                                                                                                                        |
| Characterise viral genotype                                                                                                                      | 
 
At baseline and Day 8
 
                                                                                                                                                                                                                                                                                                                                                                                                 |
| To determine the PK parameters of XVR011, following a single intravenous infusion in subjects hospitalised for COVID-19                          | 
 
Blood concentrations of XVR011 and PK parameters (<math>C_{max}</math>, AUC, <math>t_{1/2}</math>) on Days 1, 4, 8, 15, 29, 60 and 90.
 
                                                                                                                                                                                                                                                                                |
| To evaluate the immunogenicity of XVR011, following a single intravenous infusion in subjects hospitalised for COVID-19, compared to placebo     | 
 
ADAs and nAbs at baseline (Day 1 pre-dose), Day 15 and Day 29.
 
                                                                                                                                                                                                                                                                                                                                                        |

a Any form of mechanical ventilation includes but not limited to high flow oxygen therapy, continuous positive airway pressure, invasive mechanical ventilation

ADA = anti-drug antibody; AE = adverse event; AUC = area under the plasma concentration-time curve;  $C_{max}$  = maximum observed plasma concentration; COVID-2019= coronavirus disease 2019; CRP = C-reactive protein; FU = follow-up; ICU = intensive care unit; LDH = lactate dehydrogenase; nAb = neutralising anti-drug antibody; RT-qPCR = reverse transcriptase quantitative polymerase chain reaction;  $t_{1/2}$  = apparent plasma terminal elimination half-life.

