| 
Primary
 
To evaluate the efficacy of a single intravenous XVR011 infusion in subjects hospitalised for COVID-19, compared to placebo
           | 
 
Time to sustained recovery (i.e., clinical status reaching level 1 to 3 of the 8-point ordinal scale) within 28-day FU period; where recovery must be confirmed to be maintained at level 3 or lower for 14 consecutive days
 
                                                                                                                                                                                                                                                                                                                                                                                                                                                                                                                                                                                                                                                                              |
| 
Secondary
 
To further evaluate the efficacy of a single intravenous XVR011 infusion in subjects hospitalised for COVID-19, compared to placebo
 | 
 
Proportion of subjects who are alive and do not require any form of mechanical ventilation a at Day 8
 
Proportion of subjects requiring any form of mechanical ventilation a within 28-day FU period
 
Proportion of subjects requiring ICU transfer within 28-day FU period
 
Time to sustained hospital discharge (i.e. discharge with no re-hospitalisation after initial discharge for treatment of COVID-19 related events in the following 14 days) within the 90 day FU period
 
Total duration of oxygen supplementation within 28-day FU period
 
Proportion of subjects with clinical status evolving to each level of the 8-point ordinal scale at Days 2, 3, 4, 8, 15, 22 and Day 29, compared to baseline
 
Proportion of subjects with COVID-19 related symptoms
 
All-cause mortality rate within 28-day FU period
 
 |

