## **8.1 Efficacy Assessments**

### **8.1.1 Clinical Status According to 8-point Ordinal Scale**

The clinical status will be assessed at the timepoints specified in the SoA (Table 1-1 for Part 1 and Table 1-2 for Part 2), using an 8-point ordinal scale (see Appendix 2), previously used in Study NCT04280705 (Beigel et al 2020).

Recovery will be defined as achieving a clinical status  $\leq 3$  on the 8-point ordinal scale. This will be considered 'sustained recovery' if the clinical status remains  $\leq 3$  for the subsequent 14 consecutive days. Time to sustained recovery will be defined as the time between treatment administration and the first occurrence of recovery which is subsequently shown to be sustained..

Deterioration in the clinical condition of the subject such that intensive care is required will be considered a treatment failure and the end of study visit should be performed.

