### **9.4.2 Primary Efficacy Endpoint**

For Part 1, refer to the safety analyses in Section 9.4.4.

For Part 2, the primary analysis for the primary endpoint (i.e., time to sustained recovery within the 28-day FU period) will be tested using the stratified (stratification factors used at randomisation) log-rank test in the FAS (if applicable) for the comparison of the 2 treatment arms. Kaplan-Meier curves will be presented, and median time to recovery and 95% CI will be calculated based on the Kaplan-Meier estimates. The Bayesian piecewise exponential model (Ibrahim et al 2001) will be used to calculate the time variant hazard ratios and 95% CI's. In this model, the stratification factors at the time of randomisation (if applicable) will be used as covariates. In these subjects with mild to moderate COVID-19 disease, no mortality or small mortality rate is

anticipated; in case of death events, a censoring time will be imputed to handle deaths similarly to cases of no recovery by Day 29.

Further details on the methodology applied for the statistical analysis will be described in the protocol and statistical analysis plan (SAP).

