### 9.4.3 Secondary Efficacy Endpoints

Proportion of subjects who are alive and do not require any form of mechanical ventilation at Day 8. Proportion of subjects requiring non-invasive or invasive, mechanical ventilation, proportion of subjects requiring intensive care unit (ICU) transfer, and all-cause mortality rate within 28-day FU period will be presented.

Total duration (days) of oxygen supplementation within 28-day FU period, change from baseline in the nasopharyngeal viral load (RT-qPCR) will be reported as continuous endpoints.

Proportion of subjects with clinical status evolving to each level of the 8-point ordinal scale at Days 2, 3, 4, 8, 15, 22, and Day 29, compared to baseline, will be tabulated in a shift table.

Time to event secondary endpoints will be analysed using a methodology similar to the analysis of the primary efficacy endpoint.

In Part 1, the secondary endpoints will be summarised descriptively.

In Part 2, the comparison between XVR011 and placebo will be conducted for every secondary endpoint and resulting p-values will be presented.

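### The Part 2 endpoint of sustained hospital discharge has no survival condition and is tied to the initial discharge, so its literal wording misclassifies deaths soon after discharge and subjects re-admitted and later discharged for good

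*Protocol*

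**What the plan says.** The Synopsis and Table 3–2 word the endpoint, time to sustained hospital discharge, identically: "discharge with no re-hospitalisation after initial discharge for treatment of COVID-19 related events in the following 14 days", followed by the window "within the 90 day FU period". It is therefore not a slip in one table.

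For the analysis, Section 9.4.3 states: "Time to event secondary endpoints will be analysed using a methodology similar to the analysis of the primary efficacy endpoint". The same section gives every Part 2 secondary endpoint a comparison between the arms with a p-value. In the primary analysis (Section 9.4.2), "a censoring time will be imputed to handle deaths similarly to cases of no recovery by Day 29".

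The primary endpoint is defined differently. Section 8.1.1 states "This will be considered 'sustained recovery' if the clinical status remains" at level 3 or lower for the next 14 days. Time runs from treatment administration to "the first occurrence of recovery which is subsequently shown to be sustained". In Appendix 2 (Section 10.2), death is score 8. Another secondary endpoint in Table 3–2 names survival outright: "Proportion of subjects who are alive and do not require any form of mechanical ventilation" at Day 8.

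**The concern.** An endpoint that claims a discharge lasted should fail when the subject dies within the confirmation window. It should also be able to recognise a later discharge that does last. The wording does neither.

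The two gaps act in opposite ways. The missing survival condition lets a very bad outcome meet the criterion for a good one. The tie to the initial discharge can turn a short re-admission into no event at all in 90 days.

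This is the event definition itself. An SAP that added survival or accepted a second discharge would be changing the protocol's endpoint, not filling in analysis detail. If the point stays open, site staff, programmers and the SAP author could each classify these subjects differently, and a choice made after the data are seen would be post hoc.

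**Working it through.** The protocol states no figure for this endpoint, so there is none to reproduce. The check applies the definitions to two hypothetical subjects and then shows the scale under assumed rates.

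**Subject A: discharged Day 6, dies at home Day 12.**
- Sustained discharge, literal wording: the subject was discharged, and no re-hospitalisation followed in the next 14 days. Every stated condition is met, so the event is dated Day 6.
- Primary endpoint: status becomes 8 on Day 12, which is 12 − 6 = 6 days after recovery. The 14-day requirement fails, so there is no recovery event.
- Section 9.4.2 death rule: it is worded for recovery and Day 29. It is not restated for discharge or Day 90, and it does not say that a death cancels a discharge that came before it.

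**Subject B: discharged Day 4, re-admitted for COVID-19 Day 9, discharged for good Day 14.**
- Sustained discharge, literal wording: re-admission comes 9 − 4 = 5 days after the initial discharge, so that discharge fails. The wording offers no route for the Day 14 discharge. The 14 days after it end on Day 14 + 14 = Day 28, far inside the 90-day window.
- Primary endpoint: assuming the re-admission puts the subject at level 4 or above, the first recovery is broken. The Day 14 recovery, if maintained to Day 28, counts because it is the first one shown to be sustained.

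| | Literal sustained discharge | Primary endpoint |
|---|---|---|
| A (dies within 14 days) | Event at Day 6 | No event |
| B (re-admitted, then discharged for good) | No event to Day 90 | Event at Day 14 |

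**Scale, for illustration only.** Arm sizes come from Section 9.2: 272 XVR011 and 136 placebo. Assume 95% of each arm is discharged: 272 × 0.95 = 258.4 and 136 × 0.95 = 129.2. The affected number is the discharged count times the assumed rate.

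| Assumed rate among discharged subjects | XVR011 | Placebo |
|---|---|---|
| COVID-19 re-admission within 14 days, later discharged for good: 2% | 5.2 | 2.6 |
| 5% | 12.9 | 6.5 |
| 10% | 25.8 | 12.9 |
| Death within 14 days of discharge: 0.5% | 1.3 | 0.6 |
| 1% | 2.6 | 1.3 |
| 2% | 5.2 | 2.6 |

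None of these rates is in the protocol. The same rate is applied to both arms, so the difference between columns reflects only the 2:1 allocation.

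**Data needed.** Section 10.4.2 says that an event that is not an AE cannot be an SAE, and gives hospitalisation for the study disease and death from its progression as examples. After discharge, the Part 2 schedule records clinical status only at visits. After Day 29 these are 60 − 29 = 31 and 90 − 60 = 30 days apart, so a whole 14-day window can fall between two visits. SAE forms and visit status alone may therefore not supply the dates.

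**The case against.** The strongest defence is that the protocol already points to sensible handling. Section 9.4.3 carries the primary methodology over, Section 9.4.2 treats deaths as non-events, and Section 8.1.1 takes the first recovery that proves sustained. On that view a discharge is not established until its 14 days are complete, the mention of the initial discharge only says when a re-hospitalisation counts, and the remaining detail belongs in the SAP. The protocol also expects few or no deaths, Section 6.7 links discharge to improvement, and mortality to 28 days is reported separately.

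Part of this stands. It is not settled that a death after discharge would be analysed as a success, because a reader could apply the primary death rule. Nor does any text say that a re-admitted subject is censored at Day 90; that follows from the literal wording and is not a stated rule. But the carry-over is only to similar methodology, and the explicit definition says something else. Expecting few deaths limits the effect without correcting the definition.

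Two stronger readings are tempting and are not supported:
- **The wording penalises the arm discharged earlier.** Each discharged subject has the same 14 days at risk, counted from that subject's own discharge. The protocol gives no reason to expect more re-admissions under XVR011. If the drug lowered re-admission, the wording would favour it.
- **A definite number of subjects is misclassified.** Multiplying assumed rates by all 408 randomised subjects overcounts. Only discharged subjects can be affected, and a re-admitted subject who is never durably discharged is scored correctly.

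A difference between the primary endpoint and this one is also not a contradiction in itself, since recovery and discharge are different outcomes. The primary endpoint matters here because it shows that the protocol already has a workable form.

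**Conclusion.** The point holds as a fault in a stated definition. On its literal wording, sustained discharge includes subjects who die out of hospital within 14 days and excludes subjects who are re-admitted for COVID-19 and later durably discharged. Sections 9.4.2 and 9.4.3 do not clearly correct either case. The unseen SAP may settle the handling, but the protocol's definition would still read otherwise.

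The size is limited. This is one of several secondary endpoints, and the primary analysis and the sample size do not depend on it. The number affected is unknown and probably small, and the direction of any bias is unknown. The counts shown rest wholly on assumed rates and an assumed 95% discharged. The change is still worth making, because the endpoint carries a p-value between the arms and the correction is short.

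**What to change.** Replace the definition in the Synopsis and in Table 3–2 with the same text, for example:

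*Time from treatment administration (the same origin as the primary endpoint) to the first discharge, within the 90-day window, that is followed by 14 consecutive days alive and free of re-hospitalisation for COVID-19 related events. After such a re-hospitalisation, a later discharge may qualify. Subjects who die without a qualifying discharge are handled as not discharged through Day 90.*

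The origin is stated so that it matches Section 8.1.1. No separate category for end-of-life discharge is needed, because the 14 days alive already cover it.

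Confirm that discharge, re-admission (with reason) and death dates are eCRF fields through Day 90, independent of SAE reporting. If they are, the cost is one definition edited in two tables and mirrored in the SAP. If they are not, a few date fields must be added.
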